**Figure 3 F3:**
[figure not shown]
SZ-NARDS protocol time line spans from birth to three years of corrected age collecting health data and biospecimens. **(a)** MRI date will be collected if the infant is undergoing the procedure; **(b)** Cord blood, if available, will be bio banked at each participating center; **(c)** Breast milk samples will be collected if the infant is breastfed; **(d)** Tracheal aspirate samples will be collected when intubated infants require clinical suctioning. BSID-IV, the bayley scales of infant and toddler development, fourth edition; GDS-C, the griffiths developmental scales-Chinese; HINE, the hammersmith infant neurological examination; MRI, magnetic resonance imaging; NICS, neonatal intensive care severity score.

#### Clinical data and key variable definitions

3.8.1

Demographic characteristics, baseline information, and follow-up data will be systematically recorded following admission and discharge. During hospitalization, data collected will include physical examination findings, neonatal critical illness scores, diagnoses, complications, biochemical parameters, pathogen cultures, imaging results, and treatments administered. Post-hospitalization follow-up assessments will be conducted at designated time points: on day 1 (within 24 h of NARDS diagnosis), during the acute exacerbation phase (defined as the moment when the OI reaches its peak), and on day 28 (or the final day of hospitalization if shorter than 28 days). For patients who succumb to their condition or require ECMO, data will also be gathered 24 h prior to death or the initiation of ECMO. Supplementary data, including hospitalization duration and associated costs, will also be documented.

Key clinical variables were standardized to ensure consistency in reporting:
Bronchopulmonary Dysplasia (BPD) will be diagnosed at 36 weeks postmenstrual age (PMA) and its severity classified according to the NICHD 2018 workshop definition, based on the level of respiratory support required (31).Pulmonary air leak is defined as the presence of air in the lung parenchyma, detectable by radiographic imaging. This includes conditions such as pneumothorax, pneumomediastinum, interstitial emphysema, and pericardial emphysema.Severe pulmonary hemorrhage is identified when hemorrhagic fluid is aspirated through endotracheal intubation, accompanied by acute respiratory distress and clinical deterioration. Radiographic findings typically reveal involvement of more than two lung lobes, and mechanical ventilation or other interventions are required within one hour of the appearance of blood.Hemodynamically significant patent ductus arteriosus (hsPDA) is defined by echocardiographic confirmation of a ductus arteriosus with a diameter greater than 1.5 mm and a left-to-right transductal shunt (32).Severe retinopathy of prematurity (ROP) includes stages 3, 4, or 5, or when surgical intervention is necessary (33).Intraventricular hemorrhage (IVH) grade III affects more than 50% of the ventricular area and often results in lateral ventricle distention, while grade IV involves hemorrhagic infarction in the periventricular white matter.Periventricular leukomalacia (PVL) is diagnosed based on cranial imaging findings, including ultrasound, computed tomography (CT), or magnetic resonance imaging (MRI).Sepsis is classified as early-onset (within 72 h) or late-onset (after 72 h) based on the timing of bacteremia.

#### Biospecimens collection and management

3.8.2

The collection of biospecimens is a key voluntary sub-study of the SZ-NARDS cohort. Participation requires a separate, specific written informed consent from the infant's legal guardians, ensuring they are fully aware of the distinct nature of the biobanking component.

##### Ethics, consent, and incidental findings

3.8.2.1

A Standard Operating Procedure (SOP) for biospecimen handling has been approved by the lead hospital ethics committee and adopted by all participating centers (30). The biobank consent form describes the types of samples, processing methods, minimal risks, storage duration, and potential future unspecified research. A predefined policy for incidental findings (IFs), approved by the ethics committees, specifies which findings may be returned to families, the confirmation procedures in a clinical-grade laboratory, and the availability of genetic counseling. Guardians may opt in or out of receiving IFs and may withdraw consent at any time without affecting clinical care.

##### Collection, processing, and storage

3.8.2.2

Where consented and feasible, six biospecimen types-cord blood, peripheral blood, urine, stool, breast milk, and tracheal aspirates-will be collected longitudinally at standardized phases of the disease trajectory, including baseline (within 24 h of NARDS diagnosis), acute exacerbation, day 28 or prior to discharge, and long-term follow-up visits (6–36 months). Each specimen is linked to specific downstream analyses: PAXgene Blood RNA tubes for transcriptomic profiling, buffy coat for genomic analysis, plasma/serum for proteomic and metabolomic assays, and stool/urine for microbiome and metabolic phenotyping. A detailed specimen collection schedule is presented in Figure 3. They will be processed within two hours, aliquoted, assigned anonymized IDs, and stored at −80 °C in a central biobank. Standardized SOPs will be used to minimize pre-analytic variability across all centers.

##### Governance and future use

3.8.2.3

The SZ-NARDS biobank will be governed by a management committee. An independent scientific and ethics committee will also be established to review all proposals for future research using the stored samples. This structure ensures that samples are used only for scientifically and ethically sound research, such as genomic, proteomic, and biomarker analyses. All data generated from the biospecimens will be linked to the clinical data in the main registry through an anonymized code, thereby maintaining patient confidentiality.

#### Post-discharge follow-up assessment

3.8.3

Survivors will be followed at corrected ages of 6, 12, 18, 24, and 36 months. Our primary long-term outcomes are survival status, neurodevelopmental impairment (NDI), severe respiratory morbidity (SRM), and growth restriction.

##### Follow-up procedures and feasibility plan

3.8.3.1

To maximize the completeness of follow-up data, a multi-pronged strategy will be implemented. Each participating center will have a dedicated research nurse or coordinator responsible for patient tracking and communication. Families will be contacted via multiple channels (including WeChat, telephone, and SMS) for appointment reminders. To reduce the burden on families and improve adherence, research visits will be scheduled to coincide with routine high-risk infant follow-up clinics whenever possible, and a travel subsidy will be provided for study-specific visits.

##### Outcome-specific assessments

3.8.3.2

Neurodevelopmental Impairment (NDI): NDI will be defined as the presence of one or more of the following at 36 months corrected age: (1) a score <85 on any of the cognitive, language, or motor composite scales of the Bayley Scales of Infant and Toddler Development, Fourth Edition (BSID-IV); (2) a diagnosis of cerebral palsy; or (3) severe hearing or vision impairment (bilateral deafness requiring aids or blindness) (34). To capture developmental trajectories, assessments will be performed longitudinally: the Hammersmith Infant Neurological Examination (HINE) will be used at 6 and 12 months, while both the Griffiths Developmental Scales-Chinese (GDS-C) and the BSID-IV will be administered at 24 and 36 months. Audiovisual evaluations will follow the Chinese High-Risk Infant Follow-Up Protocol, including auditory brainstem response (ABR) and visual evoked potential (VEP) testing at 6–12 months and behavioral audiometry and ophthalmologic examinations at 24 and 36 months.Severe Respiratory Morbidity (SRM): SRM is defined by the need for tracheostomy, prolonged hospitalization for respiratory issues beyond 50 weeks postmenstrual age, or the requirement for supplemental oxygen, respiratory support, or respiratory monitoring, or multiple rehospitalizations for respiratory causes (35). Pulmonary function will be assessed using tidal respiratory analysis (36, 37), which evaluates parameters such as tidal volume, inspiratory/expiratory ratio, and peak tidal expiratory flow.Growth Restriction: At each visit, weight, length, and head circumference will be measured and plotted on WHO growth charts for term infants and the Fenton growth charts for preterm infants. Growth restriction will be defined as weight or length below the 10th percentile for corrected age and sex.

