#### Epidemiological and clinical characterization

2.2.1

To evaluate the prognostic performance and clinical utility of the Montreux NARDS definition within the Shenzhen cohort. This involves assessing its association with mortality, severe morbidity, and long-term neurodevelopmental impairment (NDI), thereby establishing a robust framework for subsequent deep phenotype analysis.To determine the incidence, disease burden, and clinical characteristics of NARDS in participating NICUs, and to describe the short-term mortality and morbidity of affected infants.To characterize the clinical trajectories of NARDS, including the time course from the inciting insult to key endpoints such as severe disease, the requirement for extracorporeal membrane oxygenation (ECMO), or death, and to analyze mortality patterns over a three-year follow-up period.

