### Post-discharge follow-up outcomes

4.2

Primary follow-up outcome: survival status at 36 months corrected age.Secondary follow-up outcomes: NDI, SRM, growth restriction, and loss to follow-up rates (evaluated at the 24- and 36-month assessments).

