### Statistical analysis plan

6.1

Continuous variables will be summarized as mean ± standard deviation (SD) or median with interquartile range (IQR), depending on distribution. Categorical variables will be presented as frequencies and percentages. Group comparisons will be conducted using the student's *t*-test or Mann–Whitney *U* test for continuous variables, and the *χ*² test or Fisher's exact test for categorical variables.

Univariate logistic regression will be used to examine associations between NARDS and study outcomes. Multivariable logistic regression will then be performed to identify independent predictors. Missing data will be addressed primarily using multiple imputation by chained equations (MICE), assuming data are missing at random. Variables with excessive missingness will be excluded according to predefined thresholds, and the imputation model will be structured accordingly. Sensitivity analyses will include complete-case analysis, k-nearest neighbors (k-NN) imputation, and inverse probability weighting to evaluate the robustness of findings to loss to follow-up. A two-sided *p* < 0.05 will be considered statistically significant. All analyses and visualizations will be conducted using R software (version 4.3.3).

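### Long-term NDI is assessed in survivors and analysed apart from death, and the one missing-data rule does not separate outcomes undefined by death from outcomes lost to follow-up

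*Protocol article*

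**What the plan says.** Section 3.8.3 limits long-term assessment to survivors: "Survivors will be followed at corrected ages of 6, 12, 18, 24, and 36 months". Section 3.5 ends participation at death. Section 3.8.3.2 defines impairment at one late time point: "NDI will be defined as the presence of one or more of the following at 36 months corrected age". The listed components are Bayley scores, cerebral palsy, and hearing or vision loss; death is not among them.

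Section 4.2 makes survival at 36 months the primary follow-up outcome and keeps the others apart from it: "Secondary follow-up outcomes: NDI, SRM, growth restriction, and loss to follow-up rates". Section 2.2.1 plans to relate the Montreux definition to mortality, severe morbidity and NDI, each named separately. Section 6.5 plans propensity-score comparisons of non-randomised treatments and names no outcome for them.

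On incomplete data, section 6.1 states: "Missing data will be addressed primarily using multiple imputation by chained equations (MICE), assuming data are missing at random". The sensitivity analyses are complete-case, k-nearest-neighbour imputation, and "inverse probability weighting to evaluate the robustness of findings to loss to follow-up". Death is not mentioned there. Section 6.2 gives the long-term prediction target as mortality, NDI, SRM or growth restriction, without saying whether this is one composite or four targets.

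**The concern.** A Bayley score at 36 months is not missing for a child who has died; it does not exist. The general rule in section 6.1 leaves two routes for such a child, and the article chooses neither. Imputing creates a value with no meaning. Leaving the child out conditions the analysis on survival without saying so. The listed sensitivity analyses do not help, because each treats absence as missingness or as loss to follow-up.

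This matters most for the severity question. The Introduction states that the oxygenation index correlates with both morbidity and mortality. If severe disease kills a larger share of the frailest infants, the surviving severe group is a more selected group than the surviving mild group, and the link between severity and NDI can be understated. The same mechanism can distort treatment comparisons: a treatment that improves survival changes who is left to be assessed.

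**Working it through.** **The plan's own figure.** Section 3.6.2 asks for 10 events for each of 10 predictors, so 10 × 10 = 100 deaths. At 12.6% mortality, 100 / 0.126 = 793.65, rounded up to 794. This reproduces the stated minimum.

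**How many infants are affected.** At the target of 1,000:
- 12.6% mortality (section 3.6.2): 126 deaths, 874 infants in whom 36-month NDI can be defined.
- 17% to 24% (international cohort, Introduction): 170 to 240 deaths, 830 to 760 infants.

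Any deaths after discharge not counted in these rates would add to this.

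**Two estimands, not a bias.** Assume 5% death and 20% NDI among survivors in mild disease, and 35% and 30% in severe disease.
- Survivors only: (0.30/0.70) / (0.20/0.80) = 1.71.
- Death or NDI: mild 0.05 + 0.95 × 0.20 = 0.24; severe 0.35 + 0.65 × 0.30 = 0.545; odds ratio (0.545/0.455) / (0.24/0.76) = 3.79.

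The gap arises because deaths were added. With NDI equal at 20% in both classes, severe becomes 0.35 + 0.65 × 0.20 = 0.48, and the composite odds ratio is still (0.48/0.52) / (0.24/0.76) = 2.92. So 1.7 against 3.8 shows that the choice of estimand matters; it does not measure bias.

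**A check that isolates bias.** None of these inputs comes from the document: 25% of infants severe; mortality risk ratio (RR) severe versus non-severe of 1, 3 or 5; an unmeasured binary frailty with 30% prevalence and odds ratio 1, 3 or 6 on both death and NDI; NDI risk 25% in non-severe infants; severity odds ratio for NDI 1.5 within frailty strata. Non-severe mortality is overall mortality / (0.75 + 0.25 × RR). The comparator is the odds ratio among infants who would survive at either severity.

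Worked case, mortality 12.6%, RR 5, frailty odds ratio 6:
1. Non-severe mortality 0.126 / 2 = 6.3%; severe 5 × 6.3% = 31.5%.
2. Solving for the strata (non-frail, frail): death 2.8%, 14.6% in non-severe and 19.6%, 59.3% in severe; NDI 14.3%, 50% in non-severe and 20%, 60% in severe.
3. Frail share among survivors: non-severe 0.3 × 0.854 / 0.937 = 27.4%; severe 0.3 × 0.407 / 0.685 = 17.8%.
4. NDI among survivors: 24.1% and 27.1%, odds ratio 1.17.
5. Non-severe NDI with the severe survivors' frailty mix: 0.822 × 14.3% + 0.178 × 50% = 20.6%. Against 27.1% the odds ratio is 1.43.

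| Overall mortality | RR | Frailty OR | Survivors-only OR | OR in infants who survive either way | Death-or-NDI OR |
|---|---|---|---|---|---|
| 12.6% | 1 | 6 | 1.42 | 1.42 | 1.29 |
| 12.6% | 3 | 1 | 1.50 | 1.50 | 2.21 |
| 12.6% | 3 | 3 | 1.40 | 1.47 | 2.12 |
| 12.6% | 3 | 6 | 1.25 | 1.43 | 1.98 |
| 12.6% | 5 | 3 | 1.37 | 1.47 | 2.67 |
| 12.6% | 5 | 6 | 1.17 | 1.43 | 2.48 |
| 24% | 5 | 6 | 1.07 | 1.45 | 4.81 |

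The first two rows show no bias when severity does not affect death or when no frailty is shared. The model includes no covariate adjustment, so it shows direction and possible size only.

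**The case against.** The strongest reply is that this rests on silence, in a condensed article whose full analysis plan is not shown. A reader might infer that dead infants will be given imputed Bayley scores. No passage says so. Table 1 records deceased infants, survivors and lost cases separately, and the natural reading of section 3.8.3 is that long-term morbidity is a survivor outcome. That stands: the article fails to exclude such imputation, but does not prescribe it. What remains is that the article chose to state its method, its assumption and its sensitivity analyses, and that stated rule does not fit outcomes cut off by death.

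Death is also not hidden. Survival is the primary follow-up outcome, and mortality is named first in the same objective as NDI, so a mortality gradient by severity would be reported alongside. This limits the harm but does not give the NDI estimate a defined meaning.

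Three further limits stand. Bias needs causes shared by death and NDI that remain after the adjustment in section 6.5 for gestational age, birth weight z-score, sex and major comorbidities. SRM and growth restriction are not strictly survivor outcomes, since growth is measured at every visit and some SRM components can precede a later death; the strict case is 36-month NDI. And the list in section 6.2 may be meant as a composite including death, though it covers prediction only.

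Finally, separate reporting of mortality and survivor morbidity is a legitimate choice for a descriptive registry. Replacing the separate outcomes with mandatory composites is therefore not required.

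**Conclusion.** The point holds as a gap in the stated analysis with a conditional consequence. About 126 infants per 1,000 at the planning rate, or 170 to 240 at the international rates, will have no definable 36-month NDI, and the article gives no rule that treats them differently from infants lost to follow-up. If severity raises mortality, as the Introduction supports, and shared causes of death and NDI remain after adjustment, a survivors-only or imputed severity odds ratio is probably pulled toward the null. In the illustration it falls from 1.43–1.47 to 1.17–1.40 at 12.6% mortality, and from 1.45 to 1.07 in the most extreme case at 24%. All of that rests on assumed inputs; the true size cannot be derived from the document.

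Two stronger readings are not supported. One is that the planned analysis is certain to be biased, or that treatments which save sick infants will necessarily appear to raise NDI; section 6.5 names no outcome for those comparisons. The other is that 1.7 against 3.8 measures the error; those figures answer two different questions.

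**What to change.** 1. In section 6.1, restrict imputation of 24- and 36-month outcomes to infants known or presumed alive at that assessment, and state that outcomes after death are not imputed.
2. For the severity-association analysis (2.2.1) and the treatment comparisons (6.5), add death-or-NDI at 36 months, and death-or-SRM where SRM is used. Report it beside mortality and the survivors-only result, with the latter labelled as conditional on survival.
3. In section 6.2, state whether the long-term target is one composite or four separate outcomes.

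The cost is wording and some extra tables; Table 1 already collects dates of death. The downside is that a composite mixes events of different weight and can be driven by death, as the 2.92 odds ratio with equal NDI shows. Reporting the components beside it deals with this.

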#### Inclusion and exclusion criteria

3.6.1

Neonates will be enrolled consecutively upon meeting the full set of Montreux criteria for the diagnosis of NARDS during hospitalization. This cohort will include infants of all gestational ages, including premature infants, provided their respiratory distress meets all five Montreux criteria. These criteria include: (1) an acute onset of symptoms within one week following a known or suspected clinical insult; (2) exclusion of respiratory distress attributable to neonatal respiratory distress syndrome (NRDS), transient tachypnoea of the newborn (TTN), or congenital anomalies; (3) radiological evidence of bilateral, diffuse irregularities, including reduced translucency or opacities, that cannot be explained by conditions such as pleural effusion, atelectasis, NRDS, TTN, or congenital anomalies; (4) absence of congenital heart disease as the cause of pulmonary oedema, with echocardiographic confirmation required to verify the origin of the oedema; and (5) the presence of an oxygenation deficit, categorized by the OI as mild (4 ≤ OI < 8), moderate (8 ≤ OI < 16), or severe (OI ≥ 16). All five criteria must be fulfilled for diagnosis.

Exclusion criteria include: (1) respiratory distress due to primary surfactant deficiency (e.g., hyaline membrane disease), TTN, or congenital lung malformations; (2) congenital heart disease resulting in pulmonary oedema; (3) known genetic syndromes or chromosomal abnormalities; (4) data that did not conform to the Montreux criteria or cases with unavailable outcome data; and (5) abandonment or death occurring within 24 h of birth.

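### The NDI definition does not classify a child who is seen but cannot complete any Bayley composite because of impairment and has neither cerebral palsy nor severe sensory loss; every available route tends to understate NDI

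*Protocol article*

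**What the plan says.** Section 3.8.3.2 sets the rule: "NDI will be defined as the presence of one or more of the following at 36 months corrected age". The first criterion is "a score <85 on any of the cognitive, language, or motor composite scales" of the BSID-IV. The other two are a cerebral palsy diagnosis and severe bilateral hearing loss or blindness, and neither needs a Bayley score. The same section schedules HINE at 6 and 12 months and states that "both the Griffiths Developmental Scales-Chinese (GDS-C) and the BSID-IV will be administered at 24 and 36 months". HINE and GDS-C are not part of the NDI definition.

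On missing data, section 6.1 says: "Missing data will be addressed primarily using multiple imputation by chained equations (MICE), assuming data are missing at random". It adds: "Sensitivity analyses will include complete-case analysis, k-nearest neighbors (k-NN) imputation, and inverse probability weighting", with the stated aim of checking robustness to loss to follow-up. It names neither the outcomes to be imputed nor the variables in the imputation model. Separately, the exclusion criteria in section 3.6.1 list "cases with unavailable outcome data".

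NDI is among the primary long-term outcomes in section 3.8.3 and a secondary follow-up outcome in section 4.2. It is also used to assess the Montreux definition (2.2.1) and is one target of the long-term prediction models (6.2).

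**The concern.** The three criteria form a closed list. Consider a child who comes to the visit but cannot complete any BSID-IV composite because of severe cognitive or behavioural impairment, and who has neither cerebral palsy nor severe sensory loss. The definition gives this child no status. The child has not died and is not lost to follow-up: the child was seen, and the score is absent because of the condition the score is meant to detect.

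The document leaves three routes. Read literally, no criterion is met, so the child is not NDI. Under 6.1 the score may be imputed as missing at random, an assumption that fails here unless other data in the model capture the impairment. Under 3.6.1, or in the complete-case analysis, the child is dropped. All three tend to lower the NDI rate.

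The sensitivity analyses do not test this. Complete case, k-NN and inverse probability weighting all rest on observed data, and none lets missingness depend on the unobserved impairment. Their agreement with the main analysis would not be reassuring on this point.

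What is at stake is the NDI rate among survivors. If the untestable children are concentrated among those with severe NARDS, the severity gradient that the prognostic analyses look for is also at stake.

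**Working it through.** **The plan's own figure.** The document gives no NDI rate, no untestable share and no sample size for NDI. Its only calculation, in 3.6.2, is for in-hospital mortality: 10 x 10 = 100 events, and 100 / 0.126 = 793.7, rounded up to 794. That reproduces and is unaffected by this point.

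**Inputs.**
- P, true NDI rate among survivors: 35% (assumption).
- u, share of survivors untestable because of impairment, all taken to be truly impaired: 2-5% (assumption).
- c, share of those who have cerebral palsy or severe sensory loss and so already count as NDI: 50%, with 0% as the upper case (assumption).
- Survivors, for scale: 1,000 x (1 - 0.126) = 874, from the target size and mortality rate in 3.6.2, with no other losses.

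**Formulas.**
- NDI rate in tested children: p = (P - u) / (1 - u).
- Shortfall if the unclassified children are imputed at the tested children's rate: u(1 - c)(1 - p).
- Shortfall if they are dropped: P - [(1 - u)p + uc] / [1 - u(1 - c)].
- Shortfall if they are counted as not NDI: u(1 - c).

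**Numbers.** For u = 2%, p = 0.33 / 0.98 = 33.7%. For u = 5%, p = 0.30 / 0.95 = 31.6%. With u = 2% and c = 50%, imputation loses 0.02 x 0.5 x 0.663 = 0.66 points. With u = 5% and c = 50%, it loses 0.05 x 0.5 x 0.684 = 1.71 points.

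| u | c | Imputed at tested rate | Dropped | Counted as not NDI |
|---|---|---|---|---|
| 2% | 50% | 0.66 | 0.66 | 1.00 |
| 5% | 50% | 1.71 | 1.67 | 2.50 |
| 2% | 0% | 1.33 | 1.33 | 2.00 |
| 5% | 0% | 3.42 | 3.42 | 5.00 |

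(Shortfall in percentage points.)

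Dropping the children gives almost the same answer as imputing them naively, so it matters little which of 6.1 and 3.6.1 prevails. The literal reading gives the largest error.

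**If other assessments inform the imputation.** Suppose HINE, GDS-C or a 24-month Bayley led these children to be imputed as NDI with probability 0.8. The shortfall becomes u(1 - c) x 0.2. That is 0.2-0.5 points at c = 50% and 0.4-1.0 points at c = 0%.

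**Wider range.** With u = 1-5%, c = 0-80% and p = 20-40%, naive imputation loses between 0.01 x 0.2 x 0.6 = 0.12 points and 0.05 x 1 x 0.8 = 4.0 points, or about 1 to 35 of 874 children. At c = 100% the shortfall is zero.

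**Scale against sampling error.** At 35% among 874 survivors the 95% half-width is 1.96 x sqrt(0.35 x 0.65 / 874) = 3.2 points. The shortfall is mostly smaller than that, but it is a bias with a known direction and does not shrink as the cohort grows.

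**The case against.** The strongest reply is that this is a condensed article. How an uncompleted Bayley is coded could sit in an unseen analysis plan, case report form guide or procedure manual, and section 7 says outcome assessment is harmonised through detailed SOPs. That may be so. But the article states the NDI definition in full, with its components and cut-off, and applying it as written to this child gives either no answer or an answer biased in a known direction. The reason for non-testing also has to be recorded at the visit, and a later analysis plan may be unable to recover it.

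Other parts of the reply stand and limit the point:

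- A reader might infer that every child too impaired to be tested is missed. The document does not support that. Cerebral palsy or severe sensory loss counts without a Bayley score, and a single completed composite below 85 is enough. Only the remainder is affected.
- A reader might infer that these children will be imputed from tested children and so given mostly normal results. Section 6.1 does not say that NDI is imputed or from which variables. Exclusion is equally possible, and HINE, GDS-C and earlier Bayley results could inform the model. The document does not commit to using them, however, and a child who cannot do the Bayley may also be unable to do the GDS-C at the same visit.
- A reader might infer that a large share of severe impairment is lost. The protocol defines NDI as present or absent and has no severe category, so no such share can be stated for this study.

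**Conclusion.** The gap is real but narrow. The definition does not classify a child seen but unable to complete any BSID-IV composite because of impairment, without cerebral palsy or severe sensory loss. The routes left open by 3.8.3.2, 6.1 and 3.6.1 all tend to understate NDI, and the listed sensitivity analyses cannot detect it.

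The document does not fix the size. On the stated assumptions the shortfall under imputation or exclusion is about 0.7-1.7 points with half of the untestable children already caught, and 1.3-3.4 points with none caught. It is smaller if later developmental assessments inform the imputation, and larger if the child is simply counted as not NDI. The rates used are assumptions; only the direction follows from the text. It is worth correcting because the remedy is cheap and depends on information captured at the visit, not because the NDI rate is shown to be badly wrong.

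**What to change.** Add one sentence to 3.8.3.2: a child who is seen but cannot complete the BSID-IV because of developmental, motor or sensory impairment counts as NDI. Add a case report form field giving the reason for each missing Bayley. Treat as missing only children who were not seen or were not tested for unrelated reasons, such as acute illness, refusal or lack of time.

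Reconcile 3.6.1 with 6.1, so that it is clear whether a survivor without outcome data is excluded from the cohort or retained and imputed.

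The cost is one sentence, one field and a short instruction to assessors. The downside is that the assessor must judge why a child was not tested, and that judgement can vary between centres. Enrolment was to start in January 2025, so the first 36-month visits fall in about 2028 and the field can be in place before then.

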### Control of confounding and subgroup analyses

6.5

Multivariable models will adjust for key covariates (gestational age in completed weeks, birth weight z-score, sex, major comorbidities). We will perform stratified analyses by gestational age (<32 weeks, 32–36 weeks, ≥37 weeks) and present both adjusted and stratified effect estimates. To address prematurity as a potential source of confounding and misclassification (NRDS vs. NARDS), the central adjudication committee will review all ambiguous preterm cases, evaluating the timing of respiratory failure onset, radiographic features, surfactant exposure/response, and clinical course. For non-randomized treatment comparisons (e.g., ventilation strategies, surfactant use), we will use propensity score methods (matching, inverse probability weighting) and, when appropriate, instrumental variable approaches to reduce treatment selection bias. Sensitivity analyses will include restriction to term infants and to preterm strata to evaluate effect modification by prematurity.

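### Growth restriction at 6–36 months is read off different charts for term and preterm children at the same corrected age, so chart and prematurity cannot be separated

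*Protocol article*

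**What the plan says.** The cohort mixes term and preterm infants. Section 3.6.1 states: "This cohort will include infants of all gestational ages, including premature infants". Section 3.8.3 fixes one visit schedule for everyone: "Survivors will be followed at corrected ages of 6, 12, 18, 24, and 36 months".

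Section 3.8.3.2 then sets the growth rule. "At each visit, weight, length, and head circumference will be measured", and the values are "plotted on WHO growth charts for term infants and the Fenton growth charts for preterm infants". The next sentence gives the outcome: "Growth restriction will be defined as weight or length below the 10th percentile for corrected age and sex".

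No passage says that preterm-born children change to another chart at some age, names a common reference, or plans a sensitivity analysis on one.

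The outcome carries weight. Section 3.8.3 says: "Our primary long-term outcomes are survival status, neurodevelopmental impairment (NDI), severe respiratory morbidity (SRM), and growth restriction". Section 4.2 ranks it lower: "Secondary follow-up outcomes: NDI, SRM, growth restriction, and loss to follow-up rates (evaluated at the 24- and 36-month assessments". That mismatch in rank is a separate matter. Section 6.2 makes growth restriction at 24 and 36 months one of the long-term prediction targets. Section 6.5 adjusts multivariable models for gestational age and adds: "We will perform stratified analyses by gestational age", with cut-points at 32 and 37 weeks. It also plans to examine effect modification by prematurity.

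**The concern.** Correcting age for prematurity already puts term-born and preterm-born children on one age scale. Once that is done, a second reference at the same corrected age is not needed to align the groups. It makes the cut-off depend on birth group as well as on the child's size.

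Any gap between the two charts at the 10th percentile then enters the data as an apparent difference in growth between term and preterm survivors. A model predicting growth restriction with gestational age among its inputs could partly learn which chart was used. A pooled rate would mix two definitions in proportions set by the gestational-age mix of the cohort.

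**Working it through.** **Does the rule as written apply two charts at the same age?**

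1. Visits: 6, 12, 18, 24 and 36 months' corrected age, for all survivors (3.8.3).
2. Chart: WHO if term, Fenton if preterm, at each of those visits (3.8.3.2).
3. Threshold: 10th percentile for corrected age and sex (3.8.3.2).
4. Switch to a common chart: none stated.

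At any one visit, two children with identical sex, corrected age, weight and length face two cut-offs if one was born preterm and the other at term.

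**Can the planned adjustment remove it?** Gestational age at birth determines the chart. No preterm child is read on the WHO chart and no term child on the Fenton chart, so the data cannot separate a chart effect from a prematurity effect. With gestational age in the model, its coefficient absorbs the chart effect.

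**Which analyses are exposed?** The strata in 6.5 are under 32, 32–36, and 37 weeks or more. Taking the boundary between preterm and term as 37 weeks, each stratum uses one chart, so estimates within it are internally consistent. What remains exposed:

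- rates pooled over gestational ages;
- comparisons between the term stratum and either preterm stratum;
- effect modification by prematurity;
- prediction models with gestational age as a predictor.

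**How large could it be?** The protocol states no growth-restriction rate and no distance between the charts, so there is no figure of its own to reproduce. What follows is an illustration on assumptions. Both groups have the same true growth, and 10% fall under the cut-off on the first chart. The second chart's 10th percentile lies s standard deviations higher (positive s) or lower (negative s). A single normally distributed measure is used, although the protocol's outcome is weight or length.

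Proportion flagged on the second chart: p = Φ(−1.2816 + s). Odds ratio against 10%: [p/(1 − p)] / (0.10/0.90).

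| s (SD, assumed) | p | Odds ratio |
|---|---|---|
| −0.5 | 3.7% | 0.35 |
| −0.25 | 6.3% | 0.60 |
| 0 | 10.0% | 1.00 |
| +0.25 | 15.1% | 1.60 |
| +0.5 | 21.7% | 2.50 |

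For example, at s = +0.5, Φ(−0.7816) = 0.2172, and (0.2172/0.7828)/(0.10/0.90) = 2.50.

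With an assumed 400 children per group, the chance of a nominally significant term–preterm difference (two-sided 0.05) produced by the charts alone is about 94% at −0.5, 49% at −0.25, 59% at +0.25 and above 99% at +0.5 SD.

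**After the fix.** With one reference for all, s = 0. Identical growth then gives 10% against 10%, an odds ratio of 1.0, whatever the gestational group.

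**The case against.** The best defence is that the chart sentence describes plotting, while the definition is a separate sentence that names no chart. The Discussion says that outcome assessment is harmonised through standard operating procedures, which are not shown and may state when each chart applies. An article may leave such detail to them. This has some force, but the plotting rule is tied to each visit, every visit is at 6 months' corrected age or later, and no other percentile source is named. If the intention is to use the preterm chart early and WHO later, the sentence does not say so and needs correcting anyway.

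A second objection is that the harm requires the charts to diverge at these ages, which the documents do not show. This stands. The text shows that classification can differ by birth group, not that it does, nor in which direction. A reader might infer that growth restriction will be inflated in one group. Nothing in the documents supports a direction, and the assumed range has to include zero.

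A third tempting inference is that the preterm chart stops short of 6–36 months, leaving the outcome undefined or missing for preterm survivors. The documents do not give the chart's age range, so that claim cannot be made from them, and the point does not depend on it.

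Finally, the protocol announces stratified estimates rather than a formal comparison of growth-restriction rates between strata, and within-stratum estimates are sound. That limits the reach of the problem. It does not cover pooled rates, effect modification by prematurity, or the prediction task.

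**Conclusion.** The concern holds in a bounded form. As written, section 3.8.3.2 lets the same child be classed as growth-restricted or not according to birth group, at an age where correction already makes term and preterm children comparable. Gestational-age adjustment cannot undo this. The exposure is confined to analyses that combine or compare birth groups or use gestational age as a predictor.

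The size is unknown. The range of 3.7% to 21.7% around a true 10% (odds ratios 0.35 to 2.50) rests on an assumed gap of −0.5 to +0.5 SD between the 10th percentiles, identical true growth, and a single normal measure. The significance probabilities rest in addition on an assumed 400 per group. None of these is a trial figure. The matter should be corrected because the rule is explicit, the outcome is a prediction target, and the remedy is simple.

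**What to change.** In section 3.8.3.2, state that growth restriction at all 6–36 month visits is defined against one common reference at corrected age and sex for every child, whatever the gestational age at birth. The WHO charts are already named there and can serve. State that the preterm chart is not used to define this outcome.

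The cost is one sentence. The same weights, lengths, visits and corrected ages are used, and values already recorded can be reclassified from the stored measurements.
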